### Sample selection

2.3

Patients undergoing their first‐ever specialized assessment for unprovoked seizures or epilepsy with onset after age 50, who also receive a vascular risk factor evaluation (minimum requirements are outlined in Table 1) in conjunction with their initial consultation (within 1 month), are invited to participate in a prospective one‐year trial. Individuals unable to provide informed consent and those with established progressive brain disease, that is, brain tumor or neurocognitive disorder, will be excluded. Notably, we will not exclude patients already on primary or secondary cardiovascular prevention; thus, the study will include groups for whom the benefit from the intervention may be limited.

In addition, we will conduct a system‐level register‐based cohort study based on data from the National Patient Register (NPR), which covers information on all specialized health care encounters in Sweden, and the Swedish Prescribed Drug Register (SPDR), which encompasses details of all prescribed drugs dispensed at pharmacies. Patients aged ≥50 with a first‐ever outpatient appointment to one of the participating clinics and a first‐listed diagnostic code for seizures or epilepsy (ICD‐10: R568, G40) are included. Exclusion criteria will be (i) preexisting seizures/epilepsy, as demonstrated by a registered diagnostic code for seizures (ICD‐10: R568, G40, G41) or a dispensed antiseizure medication (ATC‐code: N03) more than 3 months before the initial consultation, (ii) a registered diagnostic code for stroke or TIA (ICD‐10: I61, I63, I64, or G45 except G454) before the initial consultation, or (iii) progressive brain disease, as indicated by diagnostic codes or drug prescriptions suggestive of brain tumors (ICD‐10: C71, D33, D43, C793) or neurocognitive disorders (ICD‐10: F00‐F03, F051, G30, G318, G912; ATC code: N06D). The only difference in eligibility criteria between the intervention group and the control group will be the period of recruitment; the former will consist of patients with their initial consultation in the 2 years following the “briefing and implementation phase” of the center, whereas the control group will encompass those seen in the four preceding years at the same site.

### Outcomes

2.4

The purpose of the prospective single group trial is to assess the prevalence of vascular risk factors and the impact of screening on subsequent management and vascular risk. The primary outcome is the proportion of cases receiving pharmacological intervention following the vascular risk factor evaluation; pharmacological intervention is defined as the initiation or dose adjustment of antihypertensive agents, antidiabetic agents (including SGLT2 inhibitors used for other indications), lipid‐lowering agents, antiplatelet agents, or anticoagulants (Table 2). Secondary outcomes are as follows: (i) proportion of cases where the screening procedure uncovers previously undetected vascular risk factors, subdivided into hypertension, diabetes mellitus, moderate‐to‐severe chronic kidney disease, and atrial fibrillation, (ii) alterations in modifiable vascular risk factors at the one‐year follow‐up compared to baseline measurements, (iii) changes in SCORE2/SCORE2‐OP risk scores at the one‐year follow‐up, specifically in individuals without established cardiovascular disease, (iv) proportion of participants with adverse effects following pharmacological intervention, (v) proportion with arrythmias or QT‐prolongation captured during admissions, and (vi) proportion of participants remaining on initiated treatment at the 12‐month follow‐up.

**TABLE 2 epi412987-tbl-0002:** Variables and outcomes for the two analyses.

Variables	Primary outcome	Secondary outcomes
One‐year single group prospective analysis		
See Table 1	% with pharmacological intervention	Hypertension, diabetes mellitus, moderate‐to‐severe chronic kidney disease, atrial fibrillation, alterations in modifiable vascular risk factors compared to baseline, changes in SCORE2/SCORE2‐OP at the one‐year follow‐up, % adverse effects
Matched cohort long‐term analysis		
Demographics, vascular disease, comorbidities that can cause seizures, medical treatments	Stroke	Major adverse cardiovascular events, all‐cause mortality, stroke severity (NIHSS at stroke admission; modified Rankin Scale 3 months post‐stroke), conduction block/arrhythmia, and occurrence of recurrent seizures

The cohort study focuses on long‐term risk of vascular events, at least 5 years. The primary outcome is a registered acute stroke, measured with yearly extractions from the Swedish national stroke register (95% coverage of acute strokes in Sweden). We will also measure several secondary outcomes, including major adverse cardiovascular events, a composite measure of the variables stroke (primary outcome), myocardial infarction (ICD‐10 I21–I22 in NPR or death from myocardial infarction in the CDR), and cardiovascular death (an ICD‐10 code of I0‐I99 [diseases of the circulatory system] as the underlying cause of death). Other secondary outcomes include all‐cause mortality, stroke severity (NIHSS at stroke admission; modified Rankin Scale 3 months post‐stroke), arrythmias or conduction disorder (relevant ICD‐10/procedure codes suggestive of conduction disorder, arrhythmia or cardiac arrest^13^), and occurrence of recurrent seizures, captured by the NPR (hospital admissions [inpatient care] or emergency room visits with a seizure‐related diagnostic code [ICD‐10: R56.8, G40, or G41] as the first‐listed diagnosis). Given the interaction potential and adverse effects of several ASMs on vascular risk, we will also track ASM treatment by prescription data, as previously described.^14^

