### Objectives

1.3

This project aims to assess the impact of implementing vascular risk factor assessment (screening) in the work‐up of individuals with a new‐onset unprovoked seizure after age 50. The vascular risk assessment equals the opportunistic screening that can already be done during health visits according to Swedish guidelines. Any vascular risk factor modification after the assessment is done according to existing guidelines. We aim to assess both the proportion of patients that receive pharmacotherapy as a result of the assessment and the effect on long‐term stroke risk.

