### Intervention: Evaluating modifiable vascular risk factors

2.2

The evaluation of vascular risk factors aims to identify and manage modifiable vascular risk factors early, in line with the current ESC guidelines on cardiovascular disease prevention.^12^ Like most work‐up protocols, investigators may refrain from evaluating selected cases when such intervention is deemed inappropriate or the benefit of potential cardiovascular prevention is minimal. To promote adherence to the practice change, relevant health care staff will receive information during a 6‐month “briefing and implementation phase,” during which they can also report barriers to adherence and suggest site‐specific logistical improvements.

The examinations included in the work‐up are at the investigator's discretion to align with existing local guidelines; however, the minimum requirements are listed in Table 1. A registered nurse or a nursing associate will generally be available with each initial consultation to conduct any ordered examinations, minimizing the need for additional visits. Using composite risk assessment tools, for example, SCORE2/SCORE2‐OP, is advised to guide preventive measures in individuals without already established cardiovascular disease. Investigators are free to give lifestyle advice and prescribe medications according to local or international guidelines and to tailor treatment according to the patient's preferences; the study protocol does not specify any management strategies for identified conditions beyond what existing Swedish guidelines already recommend. Participating sites will have regular education on what the guidelines stipulate regarding blood pressure targets, lipid level targets, and smoking cessation.

**TABLE 1 epi412987-tbl-0001:** Mandatory components of the vascular risk factor evaluation.

Procedure
Family history of vascular disease
Tests/examinations (order or obtain from medical records [past 3 months])
Weight
Height
Waist circumference
12‐lead ECG
Resting and standing blood pressure
Total cholesterol
HDL cholesterol
LDL cholesterol
HbA1c
High sensitivity CRP
Serum creatinine
Urine albumin‐to‐creatinine ratio
Medical history
Atherosclerotic cardiovascular disease
Atrial fibrillation
Congestive heart failure
Diabetes mellitus
Hypertension
Kidney disease
Life‐style risk factors (smoking, exercise)

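### The single-group primary outcome is an uncontrolled proportion, so it cannot by itself show treatment resulting from the assessment; a pre/post dispensing outcome in the planned register cohort could estimate that effect

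*Protocol article*

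**What the plan says.** The Objectives section of the protocol article sets the short-term aim as "the proportion of patients that receive pharmacotherapy as a result of the assessment". The Outcomes section gives the purpose of the single-group trial as assessing, besides risk factor prevalence, "the impact of screening on subsequent management and vascular risk".

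The outcome meant to serve this is in the same section: "The primary outcome is the proportion of cases receiving pharmacological intervention following the vascular risk factor evaluation". The definition follows: "pharmacological intervention is defined as the initiation or dose adjustment of antihypertensive agents", and likewise of antidiabetic, lipid-lowering and antiplatelet agents and anticoagulants. For the antidiabetic class it adds "including SGLT2 inhibitors used for other indications".

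On who is counted, Sample selection says "we will not exclude patients already on primary or secondary cardiovascular prevention". Trial participants must have received the evaluation and given consent, and the Intervention section allows that "investigators may refrain from evaluating selected cases".

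The Data analysis plan gives this outcome a normal-approximation 95% confidence interval for a proportion and no comparison. The Sample size calculation sizes it for precision: 385 patients for a margin under 5 points at an assumed 50%.

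The cohort study plans to use the Swedish Prescribed Drug Register, "which encompasses details of all prescribed drugs dispensed at pharmacies", with controls from the same sites in the four preceding years. Its outcomes (Outcomes section and Table 2) include no start of a cardiovascular drug. The Data analysis plan uses such prescriptions only as covariates and to define subgroups.

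**The concern.** The objective is causal, while the outcome is defined only by timing. A drug started or adjusted after the evaluation counts whether or not a screening finding prompted it. Three features let background prescribing in: no link to a finding is required, routine titration in patients already on prevention qualifies, and SGLT2 inhibitors given for other reasons qualify. The protocol itself notes, under Ethics and Dissemination, that opportunistic vascular risk assessment at health contacts is already advised in Sweden, so a background rate of zero is not plausible.

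If the raw percentage is reported as the impact of screening, it will overstate that impact by an unknown amount. It also leaves a gap between the two parts of the project. The pathway is that screening leads to more treatment and more treatment to fewer strokes, and its first step is not compared between the two periods. If the stroke comparison shows no difference, it will be hard to tell whether screening changed treatment too little or whether added treatment did not prevent strokes.

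**Working it through.** **Inputs from the protocol article**

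- Single-group trial: n = 385, margin 5 points, assumed proportion 50% (Sample size calculation).
- Cohort study: up to 2000 post-period and 4000 pre-period patients; the stated requirement is 1021 and 2045 (same section).
- Background rate of starts or dose adjustments: not given. Assumed here at 10%, 20%, 30% and 40%.

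**Step 1. The plan's own figure**

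n = 1.96² × 0.5 × 0.5 / 0.05² = 384.15, rounded up to 385. The half-width at 385 is 1.96 × √(0.25/385) = 4.99 points. The figure reproduces. An observed 50% would have a 95% interval of 45.0% to 55.0%, whatever the background rate.

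**Step 2. What an observed 50% would mean**

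Excess = observed proportion − background proportion.

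| Assumed background | Excess at an observed 50% |
|---|---|
| 10% | 40 points |
| 20% | 30 points |
| 30% | 20 points |
| 40% | 10 points |

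The excess spans 30 points over this range, against a confidence interval 10 points wide. The unknown background therefore matters more than the sampling error for which the trial was sized. The primary outcome states no time window of its own; over a window shorter than the one-year follow-up, the background would be lower.

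**Step 3. What the planned register cohorts could estimate**

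Half-width of the risk difference = 1.96 × √(p₁(1−p₁)/n₁ + p₀(1−p₀)/n₀), with p₁ = 50% carried over for illustration. The minimum detectable increase over background is for 80% power at two-sided 5%. All results are in points.

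| Background | Half-width, 2000 vs 4000 | Half-width, 1021 vs 2045 | Detectable, 2000 vs 4000 | Detectable, 1021 vs 2045 |
|---|---|---|---|---|
| 10% | 2.4 | 3.3 | 2.4 | 3.4 |
| 20% | 2.5 | 3.5 | 3.1 | 4.4 |
| 30% | 2.6 | 3.7 | 3.6 | 5.0 |
| 40% | 2.7 | 3.7 | 3.8 | 5.3 |

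**Step 4. A modest effect: 30% against 25% (both assumed)**

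Power = Φ((0.05 − 1.96 × SE₀)/SE₁), with SE₀ from the pooled proportion and SE₁ unpooled.

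- 2000 vs 4000: SE₀ = 0.01211, SE₁ = 0.01232, so Φ(2.13) = 98%. Half-width 1.96 × 0.01232 = 2.4 points.
- 1021 vs 2045: SE₀ = 0.01695, SE₁ = 0.01724, so Φ(0.97) = 83%.

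Steps 3 and 4 describe an added outcome. They show that the planned cohorts are large enough for it, and they do not measure an error in the plan.

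**The case against.** The strongest reply is that the descriptive design is declared. The trial is called single-group throughout, the outcome is worded by sequence, the analysis is a confidence interval, and the sample size is set for precision. No causal test is attached to it, and the system-level contrast belongs to the cohort study. Evaluated patients are also a proper denominator for the yield of screening. All of this stands. It places the fault in the causal wording of the Objectives section and the stated purpose in the Outcomes section, and rewording both would remove the contradiction. It would still leave the effect on treatment unestimated.

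The reply also limits how far the point can be taken. A reader might infer any of the following, and the documents do not support them:

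- *That the percentage is meaningless and the mechanism goes unexamined.* Secondary outcomes cover previously undetected risk factors, change in modifiable risk factors, change in SCORE2/SCORE2-OP, and persistence on started treatment. The analyses are also stratified by previously established risk factors. These are uncontrolled too, but they bear on the mechanism.
- *That dose reductions are counted by design.* The definition gives no direction. It does not exclude reductions, but it does not name them either.
- *That the selected denominator inflates the proportion.* This is plausible where investigators refrain because little benefit is expected, but selection by consent could act in either direction.
- *That the register data are already in hand.* They are a planned source; the ethics application awaits funding.

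**Conclusion.** The point holds as a mismatch between objective and outcome. The proportion planned for the single-group trial cannot by itself deliver the stated aim of treatment resulting from the assessment, because background starts and titration count as events and nothing in the trial estimates them. Its size is unknown from the documents. The excess of 40 down to 10 points behind an observed 50% rests wholly on the assumed 10% to 40% background.

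The figure of 385 is right, and neither primary analysis is invalidated. A reader might go further and infer that a pre/post dispensing difference would prove causation. It would not: prescribing may drift between the two periods, a weakness that the planned stroke comparison already shares. It would, however, replace an unknown background with a measured one, to within about 2.4 to 3.7 points under the assumptions above.

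**What to change.** 1. Add a secondary outcome to the cohort study: first dispensing, within 12 months of the initial consultation, of a new class among antihypertensive, lipid-lowering, antidiabetic, antiplatelet and anticoagulant drugs. Compare post-period with pre-period patients inside the register cohort, not trial participants with historical controls.
2. Base any statement about the effect of screening on treatment on that contrast, and name secular prescribing trends as its limitation.
3. Reword the Objectives and Outcomes sections so that the single-group proportion is descriptive: treatment following the evaluation among evaluated, consenting patients.
4. In the single-group trial, report initiations, dose increases and dose reductions separately.

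The cost is one extra analysis of register data that the study already plans to obtain, plus changes of wording and reporting. No additional recruitment is needed. By the protocol article's own account, registration and the ethics application still lie ahead.

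The register outcome has two further limits. It captures initiations but not intensification of existing treatment. It also applies to the cohort population, which excludes prior stroke or TIA, whereas the trial's stated criteria do not.

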### Background

1.1

Cerebrovascular disease is the most common cause of epilepsy after middle age. Interestingly, seizures can also precede stroke.^1^, ^2^, ^3^, ^4^, ^5^ UK primary care data indicated a nearly threefold increased risk of stroke after a first seizure in those aged ≥60 years,^4^ a finding that was recently replicated in Swedish population wide register data, albeit with a slightly lower risk (HR 2.27, 95%CI: 1.87–2.75).^1^ The relative increase in risk was greater for intracerebral hemorrhage (HR 2.51, 95%CI: 2.08–3.04) than ischemic stroke (HR 1.68, 95%CI: 1.56–1.80).^1^ Vascular risk factors increase the risk of late‐onset epilepsy,^6^ so a plausible explanation is that late‐onset seizures reflect occult cerebrovascular disease that has not yet resulted in a clinical stroke. This notion is further supported by a higher prevalence of silent cerebrovascular disease on imaging in patients with late‐onset seizures than in healthy controls.^7^ The highest increase in stroke risk is seen in the first year following the first seizure.^1^ Another contributing factor could be detrimental effects of antiseizure medications (ASM) on vascular risk prevention, like interactions with lipid‐lowering drugs.^8^

Given the emerging evidence of increased stroke risk after late‐onset seizures, the potential benefits of vascular risk factor management in such patients are being discussed,^7^, ^9^ but evidence on the optimal nature and effect of these interventions is lacking. In addition to stroke, other cardiac events like arrythmias or sudden cardiac death are associated with epilepsy or ictogenic mechanisms^10^, ^11^ but whether vascular risk factor intervention mitigates such risks is unknown. Current clinical practice does not consider vascular risk factors in management of first seizures. It is simply not known whether detection and treatment of hypertension and/or optimization of serum lipids is beneficial or not in this patient group.

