### Data analysis plan

2.5

Descriptive statistics will be presented as median (interquartile range) or number (%). For the single group study, we will use the normal approximation method to calculate 95% confidence intervals for proportions, including the primary outcome. Comparisons between baseline and one‐year follow‐up measurements will involve paired analyses, for example, McNemar's test for categorical data and paired t‐test or a non‐parametric equivalent for continuous data, depending on the data distribution. The analyses will be stratified by age groups, sex, and previously established cardiovascular risk factors. All tests will be two‐sided and considered statistically significant at *p* < 0.05.

The cohort study examines time to the different events of interest. We will use the Kaplan–Meier method and Cox proportional hazards regression to evaluate all‐cause mortality. For other events of interest, death will be accounted for as a competing risk. Survival times are calculated from the initial consultation until either the event of interest, death or study end, whichever comes first. To compare baseline group differences, we will utilize the Fisher exact test, the *χ*
^2^ test, or the Mann–Whitney *U* test, depending on the data characteristics. We do not anticipate any significant group differences; however, we will perform univariable and multivariable regression analyses to identify and adjust for any relevant covariates (age, sex, medical history, prescriptions of drugs used for cardiovascular prevention). Subgroup analyses will comprise previously “healthy” individuals (no drug prescriptions related to cardiovascular prevention) and individuals without established cardiovascular disease (defined as not being prescribed antiplatelet agents or anticoagulants). Analyses will also be stratified by age groups and sex.

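### The cohort's arrhythmia/conduction outcome is counted from the consultation at which only the intervention period has a standard ECG, so screen-detected disease can count as an early event and bias the comparison against the intervention

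*Protocol article*

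**What the plan says.** All references are to the Protocol article.

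- **Outcome.** Outcomes (2.4) lists arrhythmia or conduction disorder among the cohort study's secondary outcomes, identified by relevant ICD-10 or "procedure codes suggestive of conduction disorder, arrhythmia or cardiac arrest" with a cited source for the codes. No care setting, diagnosis position or rule for earlier codes is stated.
- **Time zero.** Data analysis plan (2.5): "Survival times are calculated from the initial consultation until either the event of interest, death or study end, whichever comes first". No blanking period is given.
- **Screening.** Table 1 (Intervention, 2.2), titled "Mandatory components of the vascular risk factor evaluation", includes a 12-lead ECG. For patients invited to the one-year trial, Sample selection (2.3) places the evaluation "in conjunction with their initial consultation (within 1 month" of that visit.
- **Comparison.** Sample selection states that "the control group will encompass those seen in the four preceding years at the same site", and that "The only difference in eligibility criteria between the intervention group and the control group will be the period of recruitment". Exclusions are earlier seizures, stroke or TIA, and progressive brain disease. Earlier arrhythmia is not among them.
- **Usual care.** Background (1.1): "Current clinical practice does not consider vascular risk factors in management of first seizures".

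**The concern.** The intervention is itself a detection step for part of this outcome. An ECG done at or just after time zero can reveal atrial fibrillation or conduction block that was already present. Once coded in specialised care, it can enter the National Patient Register as an event in the first weeks of follow-up. Control-period patients had no such standard work-up, so the same disease in them would be coded later or not at all.

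The single-group trial lists newly uncovered atrial fibrillation as a screening yield. In the cohort comparison the same finding would count against the practice change. Effective screening could then look like more arrhythmia, or a real reduction could be hidden. Adjusting for medical history, as section 2.5 plans, does not help, because disease not yet detected has no earlier code to adjust for.

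**Working it through.** **Step 1: compare the outcome definitions.**

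| Outcome | Limit stated |
|---|---|
| Cohort: stroke (primary) | Acute stroke in the national stroke register |
| Cohort: recurrent seizures | Admissions or emergency visits, first-listed code |
| Single-group trial: arrhythmia or QT prolongation | Captured during admissions |
| Cohort: arrhythmia/conduction disorder | None stated |

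Of these four, only the last could, as worded, be met by an outpatient code from the screening visit. Section 2.3 says the National Patient Register covers all specialised encounters, so such a code would be available to count.

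**Step 2: inputs for an illustration.** The plan gives no figure for this outcome, so there is none to reproduce.

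- Group sizes from Sample size calculation (2.6): 1021 post and 2045 pre (required); up to 2000 and 4000 (expected). As a check on the required size, 7% v 10% with 1:2 allocation, two-sided 0.05 and 80% power gives 1038 and 2076 by the pooled two-proportion formula, within 2% of the stated numbers.
- Two-sided 0.05, from section 2.5.
- *Assumptions, not in the documents:* control cumulative risk p0 of 5%, 10% or 20%; excess detection d of 0.5% to 3%. Here d is the additional share of intervention-period patients coded because of screening, not the full prevalence of hidden disease.

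**Step 3: formulas, with no true effect.**

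- Intervention-period risk: p1 = d + (1 − d) × p0. Apparent risk ratio: p1/p0.
- Probability of a significant excess: Φ[(p1 − p0 − 1.96 × SE0)/SE1], where SE0 uses the pooled proportion and SE1 the separate ones. This two-proportion test stands in for the planned competing-risk analysis.

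Example, d = 2% and p0 = 10%: p1 = 0.02 + 0.98 × 0.10 = 0.118, ratio 1.18.

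- 2000/4000: SE0 = 0.00843, SE1 = 0.00863; (0.018 − 0.01652)/0.00863 = 0.17; probability 57%.
- 1021/2045: SE0 = 0.01180, SE1 = 0.01208; (0.018 − 0.02312)/0.01208 = −0.42; probability 34%.

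**Step 4: range.**

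| p0 | d | Risk ratio | False excess, 1021/2045 | False excess, 2000/4000 |
|---|---|---|---|---|
| 5% | 0.5% | 1.10 | 8.4% | 12.3% |
| 5% | 1% | 1.19 | 20.3% | 34.4% |
| 5% | 2% | 1.38 | 57.2% | 84.1% |
| 5% | 3% | 1.57 | 86.6% | 98.9% |
| 10% | 0.5% | 1.05 | 5.9% | 8.0% |
| 10% | 1% | 1.09 | 12.1% | 19.3% |
| 10% | 2% | 1.18 | 33.6% | 56.8% |
| 10% | 3% | 1.27 | 61.4% | 87.8% |
| 20% | 0.5% | 1.02 | 4.5% | 5.6% |
| 20% | 1% | 1.04 | 7.6% | 11.0% |
| 20% | 2% | 1.08 | 17.9% | 30.5% |
| 20% | 3% | 1.12 | 34.0% | 57.8% |

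The nominal rate in this direction is 2.5%.

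**Step 5: two variations at p0 = 10%.**

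- *Catch-up in controls.* If half of a hidden 2% is coded in controls during follow-up (assumption), the net gap is about one percentage point. For 11% v 10% the ratio is 1.10, and the false-excess probability is 23% (2000/4000) or 14% (1021/2045).
- *Masking.* Suppose a true 30% reduction, borrowing the effect the protocol assumes for stroke. Then p1 = d + (1 − d) × 0.07, and the ratio appears as 0.79, 0.89 and 0.98 for d of 1%, 2% and 3%, instead of 0.70.

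**The case against.** The strongest reply is that silence is being read as a rule. The article refers to a cited source for the codes, and that source or a fuller protocol might set the care setting, diagnosis position and handling of prevalent cases. This is fair, and it limits the point to the outcome as worded. A code list alone, however, would not change the time-zero rule in section 2.5, and the article does spell out the setting for recurrent seizures.

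Exposure to screening is also incomplete. Investigators may omit the evaluation in selected cases, Table 1 accepts results from the previous three months, and the one-month window is stated for trial invitees only. These facts reduce d but do not remove it.

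Three stronger readings are tempting and are not supported:

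- *Hidden arrhythmia stays uncoded in controls.* The documents do not say how often controls had an ECG. Not considering vascular risk factors is not the same as doing no ECG. Follow-up of at least five years also gives time for hidden disease to surface.
- *The plan scores screening as harm.* The outcome is one of several secondary outcomes and is not labelled a safety endpoint. The single-group trial separately reports newly found atrial fibrillation, which would help readers interpret an early excess.
- *A false excess is more likely than not.* Simply adding 2 points to 10% (12% v 10%) gives 65% and 40% for the two group sizes. That is an upper case: it ignores overlap with events that would have been coded anyway, and any catch-up in controls.

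**Conclusion.** The point holds in a limited form. Under the stated rules, the standard ECG in one period can generate early outcome codes that the other period lacks. The direction is against the intervention, or towards hiding a benefit. The effect is confined to this secondary outcome; acute stroke, the primary outcome, is not affected by this route.

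The size cannot be determined from the documents. Across the assumed ranges it runs from negligible (ratio 1.02) to large (1.57), and any catch-up in controls brings it down. The conclusion also assumes that the unseen code source does not already confine the outcome to acute care.

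**What to change.** Before register data are extracted, define this outcome identically in both periods as a hospital admission or emergency visit with a first-listed arrhythmia or conduction code, plus device procedures and cardiac arrest. The setting and position rule is the one section 2.4 already uses for recurrent seizures, so it needs no new register fields and no more patients. Report outpatient codes in the first three months separately by period, as detection yield.

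A three-month landmark should be a sensitivity analysis only. It changes time zero and the population analysed. Excluding patients coded before the landmark would remove screen-detected cases mainly from the intervention period, while similar undetected cases stay in the control group, which could reverse the bias.

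The cost is that some true arrhythmias diagnosed in outpatient care no longer count. Device procedures prompted by screening may also leave some residual bias.

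### As defined, two secondary outcomes of the cohort study can count contacts that are not new events: planned admissions as seizure recurrences, and re-coded known arrhythmia as arrhythmia events

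*Protocol article*

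**What the plan says.** Both outcomes are secondary outcomes of the register-based cohort study (protocol article, section 2.4, Outcomes).

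- **Recurrent seizures** are "captured by the NPR (hospital admissions [inpatient care] or emergency room visits", with R56.8, G40 or G41 "as the first‐listed diagnosis".
- **Arrhythmia or conduction disorder** is identified by "relevant ICD‐10/procedure codes suggestive of conduction disorder, arrhythmia or cardiac arrest". The code list is left to a citation.
- **Cohort entry** (section 2.3, Sample selection): patients aged 50 or over with a first outpatient appointment at a participating clinic and "a first‐listed diagnostic code for seizures or epilepsy (ICD‐10: R568, G40) are included".
- **Cohort exclusions** (section 2.3): earlier seizures or epilepsy, progressive brain disease, and "a registered diagnostic code for stroke or TIA (ICD‐10: I61, I63, I64, or G45 except G454) before the initial consultation". Earlier arrhythmia is not among them.
- **Time scale** (section 2.5, Data analysis plan): "Survival times are calculated from the initial consultation until either the event of interest, death or study end, whichever comes first".
- **Adjustment and subgroups** (section 2.5): regression is to "identify and adjust for any relevant covariates (age, sex, medical history, prescriptions of drugs used for cardiovascular prevention". Subgroups comprise people with no drugs for cardiovascular prevention, and people prescribed neither antiplatelets nor anticoagulants.

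**The concern.** A time-to-event outcome should fire when something new happens to the patient. Each of these definitions can also fire on a contact that reflects continuing care for a condition already known at time zero.

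The comparison is between calendar eras at the same clinics. Non-events that are equally common in both eras pull the result toward no difference. Non-events whose frequency changes over time, for reasons unrelated to the screening programme, appear as a difference between eras. In either case the recurrence and arrhythmia results would be hard to interpret.

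**Working it through.** **Recurrent seizures: the definition.** The entry codes are R56.8 and G40; the outcome codes are R56.8, G40 and G41. The entry codes are thus a subset of the outcome codes, and G40 is the epilepsy diagnosis itself. The code alone cannot separate a new seizure from later care of the same epilepsy, so the type of contact has to do so. For outpatient care it does, because only emergency visits count. For inpatient care no such condition is set, so a planned stay with G40 listed first, for investigation for instance, meets the rule.

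**Recurrent seizures: illustration.** The plan states no figure for this outcome, so there is none to reproduce. Assumed inputs, none from the documents: true recurrence s = 0.30 in both eras (no effect); among the rest, a share p0 = 0.10 in the control era and p1 in the intervention era have a planned admission only.

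Ratio under no effect = [s + (1 − s)·p1] / [s + (1 − s)·p0]. The denominator is 0.30 + 0.70 × 0.10 = 0.370.

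| p1 | Numerator | Ratio |
|---|---|---|
| 0.10 (unchanged) | 0.30 + 0.070 = 0.370 | 1.00 |
| 0.05 (halved) | 0.30 + 0.035 = 0.335 | 0.91 |
| 0.15 (up by half) | 0.30 + 0.105 = 0.405 | 1.09 |

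The direction depends entirely on how the use of planned admissions moves over time, which the documents do not say.

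**Dilution when the eras are alike.** Let f be the share of counted control-era events that are not new and that the intervention does not affect. A true ratio r is then observed as r(1 − f) + f. With r = 0.70, borrowed from the 30% reduction that section 2.6 assumes for stroke:

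| f | Observed ratio |
|---|---|
| 5% | 0.715 |
| 10% | 0.73 |
| 20% | 0.76 |
| 50% | 0.85 |

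In the seizure example, f = 0.070 / 0.370 = 19%.

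**Arrhythmia: the passages side by side.**

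1. For the primary outcome, patients with an earlier stroke or TIA code are removed. The three cohort exclusions contain no counterpart for arrhythmia.
2. For the one-year trial, section 2.4 counts atrial fibrillation only when the screening newly detects it. The cohort definition has no such condition.
3. The clock starts at the initial consultation, and any relevant code can stop it. The text shown requires no first-ever code, lookback, care setting or diagnosis position.
4. Known cases can be present: the subgroup without antiplatelets or anticoagulants implies that the whole cohort includes people taking them, and section 2.3 says that the patient register holds all specialized contacts.

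**Arrhythmia: illustration.** Assumed inputs, none from the documents: 8–20% known at entry, 90% of these coded again during follow-up, 6–10% new cases among the rest, and again r = 0.70.

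- Low end (8% known, 10% new): known 0.9 × 0.08 = 0.072; new 0.92 × 0.10 = 0.092; f = 0.072 / 0.164 = 44%; observed ratio (0.072 + 0.7 × 0.092) / 0.164 = 0.83.
- High end (20% known, 6% new): known 0.9 × 0.20 = 0.180; new 0.80 × 0.06 = 0.048; f = 0.180 / 0.228 = 79%; observed ratio (0.180 + 0.7 × 0.048) / 0.228 = 0.94.

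If known cases were never coded again, f would be 0 and nothing would be diluted.

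**The case against.** **The arrhythmia half rests partly on silence.** The code list is deferred to a citation, and a full protocol could add a lookback. This stands as a limit. The article does, however, list the cohort exclusions and give the time rule, and under those a known case remains at risk.

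**Section 2.5 already gives some protection.** Medical history is a candidate covariate, and the subgroup without antiplatelets or anticoagulants drops known atrial fibrillation treated with those drugs. This also stands, in part. Adjustment does not change what counts as an event, the subgroup is not the main analysis, and untreated patients or pacemaker carriers can remain in it.

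**The seizure rule is already restrictive.** It leaves out ordinary outpatient visits and requires the first-listed position. That is true, and it shows an intent to exclude routine care which the inpatient half does not carry through.

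**Removing known arrhythmia may sharpen another bias.** The new work-up has a mandatory 12-lead ECG (Table 1). Arrhythmia that it uncovers would count as new in the intervention era only, and would form a larger share of the remaining events. This stands, and the fix has to deal with it.

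**Stronger readings that the documents do not support.** A reader might infer that most counted arrhythmia events would not be new, or that a benefit on arrhythmia would be largely hidden. The documents give no prevalence, re-coding or incidence figure, and the protocol assumes no effect on arrhythmia; section 1.1 calls the effect on cardiac events unknown. A reader might also infer that planned stays crowd into the weeks after the first consultation, or that their use has fallen over the years. The documents say neither.

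**Conclusion.** The concern holds for these two secondary outcomes and goes no further. The primary outcome comes from the stroke register, in a cohort cleared of earlier stroke and TIA, and the sample size in section 2.6 concerns stroke only. Neither is affected.

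The seizure half is the firmer of the two, because its rule is written out and the gap is visible in it. The arrhythmia half holds as the text reads, subject to the cited code list and with partial cover from the planned adjustment and subgroup.

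The size cannot be derived from the documents. Under the seizure assumptions, the ratio with no effect is 1.00 if the planned-admission share is stable and 0.91 if it halves. The arrhythmia figures show the mechanism only and are not an estimate. A clear definition change is warranted.

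**What to change.** 1. **Recurrent seizures.** Count an admission only when it is unplanned: by admission type if the register extract holds that field, otherwise by entry through an emergency visit. Leave the emergency-visit part of the rule as it is.
2. **Arrhythmia and conduction disorder.** Analyse first-ever events among patients with no such code or device procedure before the initial consultation. Keep cardiac arrest as an event for everyone.
3. **Sensitivity analysis for screening detection.** Repeat the arrhythmia analysis leaving out codes from the work-up window in both eras. The first month is a natural example, since section 2.3 places the evaluation for trial participants within that time. State how a diagnosis first coded in the window and coded again later is handled. This lessens the imbalance from the mandatory ECG but may not remove it.

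**Cost.** Fewer counted events for both outcomes, since planned stays no longer count and known arrhythmia cases leave the risk set. The work is a few lines of definition and one added analysis. It can be settled before the study starts: section 3 says that the ethics application will be submitted only once funding has been obtained.
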